*Interpretation:* Pharmacokinetic models will be fitted to concentration-time and concentration-effect data from studies (a) and (c) using NONMEM (v. 5)51, to provide population parameter estimates, mean parameter values and their between-subject variability where possible. This analysis will include assessment of possible covariate relationships, where parameter values such as clearance may be correlated with patient demographics such as age. A model will be developed that describes the time course of effects of arginine in terms of NO production (plasma NOx/creatinine ratio [systemic NO production] and exhaled NO [pulmonary NO production]), oxidant stress, endothelial function, microvascular flow and gas transfer/physiological deadspace. It is also intended to address biomarkers of effectiveness. **[name] from NIHRD will be invited to the Dept Pharmacy in Brisbane to join the NONMEM modeling for the PK-PD relationships outlined above.**

Safety data from study 2 will be reviewed by an experienced independent data monitoring committee (see appendix) before proceeding to study 3. The pharmacokinetic-pharmacodynamic model developed in study 2 will enable us to predict the dosing and best sampling schedule (both pharmacokinetic and pharmacodynamic) for use in study 3. If the pharmacokinetic-pharmacodynamic model suggests that a higher dose than 12g may be required, a dose of up to 18 g may tested in stage 2 of the study prior to commencing stage 3.

*Potential adverse effects (in study 2 and study 3) and study response:* A number of adverse effects have been previously noted with large *supraphysiological* dosing in subjects with normal plasma arginine levels. These have been infrequent and usually at the standard high dose (≥30g) required to stimulate growth hormone release, **a *dose that will not be used in our studies.*** Arginine is a natural product that has been widely used in subjects with cardiovascular disease, sickle cell disease, and sepsis, with an excellent safety profile. This study primarily examines pharmacokinetic-pharmacodynamic modeling, but will also confirm safety in uncomplicated malaria.

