**Patients with uncomplicated malaria in Indonesia have mean levels of arginine *below* normal, and combined with a dose well below the standard 30g IV dose used in other settings, we do not expect significant adverse effects to occur. Whilst we believe the following adverse effects to be very unlikely, our protocol allows us to detect, and if necessary rectify them:**

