- *Effect on K+:* Hyperkalemia may result from redistribution of K+ from intracellular fluid to extracellular fluid. In seven of eight normal Italian subjects receiving high dose arginine (30g IV), mean plasma K+ transiently increased by 1.23± 0.17 meq/L (range 0.6-1.7), peaking at 60-90 mins after start of a 30 min IV infusion54. These data excluded one subject who had a “virtually negligible” increase54. Clinically significant hyperkalemia has been reported with large supraphysiological doses in patients with renal failure (30g IV)55 and combined liver failure/renal impairment (again with very high dosing of 59-95g IV)56, in subjects taking spironolactone (an exclusion criterion in this study). Mean plasma K+ in 58 Indonesian subjects with uncomplicated malaria (in our initial NO studies in Jayapura) is at the low end of normal range (3.4 meql/L), with only 1 subject out of 58 having a K+> 4.0 [4.5 meq/L]. Subjects with renal failure or baseline K+≥4.2 meq/L will not be included in studies 2 and 3. Moreover lower doses will be used in both of our studies than the 30g dose used in published studies. Therefore a rise in K+ to ≥ 6.0 meq/L will be very unlikely.

Response: If serum K+ rises to ≥ 6.0 meq/L it will be immediately repeated using the bedside iSTAT to exclude hemolysis of sample. If K+ ≥ 6.0 meq/L or if significant ECG changes of hyperkalemia develop, the infusion will be stopped and subjects will be given 10ml of 10% calcium gluconate for membrane stabilization. This will be followed by continuous ECG monitoring and 10-15 minutely monitoring of K+: if thought necessary by the attending clinician, 10 U of regular insulin will be administered with 25g of IV glucose to induce K+ shift into cells.

- *Hypophosphatemia:*

A clinically insignificant transient fall in serum phosphate is noted with 30g infusions, with the maximum fall below baseline of 1.11 mg/100ml (or 33%), peaking 60 mins after commencement of a 30 min infusion54. In no cases did phosphate levels fall to potentially clinically significant levels (<1 mg/dL)54. We will nevertheless measure phosphate levels at baseline and at 60 mins.

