*b) Effect on pH:* Arginine hydrochloride contains H+ ions (4.75 mEq/g). While there is a *theoretical* potential for acidosis there have been no reports of this. Hertz *et al* (1972) 56 carefully documented the effect of IV arginine on arterial pH. They found **no change** in the pH despite infusion of 30g (much higher than we will use in this study) and despite the fact they infused arginine into patients with renal failure – who are at risk for acidosis56. Clinically significant change in pH has not been found except in patients with hypochloremic alkalosis (where arginine hydrochloride corrects the Cl deficiency and returns the alkalosis toward normal). We therefore do not expect any acidosis, but will monitor serial real-time venous pH, PCO2, chloride and bicarbonate at the bedside using iSTAT EC8+ cartridges.

Response: Arginine infusion will be ceased if venous bicarbonate falls below 15 mmol/L.

*c)* *Effect on kidney function:* We can find no case reports or primary clinical studies that report renal toxicity with L-arginine. In fact, two recent studies show that renal blood flow and glomerular filtration rate (the most accurate measure of renal function) **improve** after the infusion of L-arginine. Schlaich et al,59 studied patients with normal renal function and used an intravenous infusion of L-arginine at doses of 100mg/kg (7 Grams for a 70 kg adult) and 500mg/kg (35 grams for a 70 kg adult) over 30 minutes. They showed a statistically significant ***improvement*** in both renal blood flow and glomerular filtration rate at each dose. In the second study60, n intravenous dosage of 17mg/kg gave the same improvement in normal subjects. Reassuringly, in patients with renal impairment in this study, arginine infusion was safe and **did not** cause any worsening of renal blood flow or glomerular filtration rate. We therefore do not expect any change in renal function in studies 2 and 3, but we will monitored renal function by serial iSTAT bedside biochemistry (see Table 2).

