**Study 3:**

***Randomised concentration controlled trial, safety, and pharmacokinetic study in uncomplicated malaria:***The pharmacokinetic-pharmacodynamic model [from studies 1 and 2)] will be used to determine an appropriate loading and maintenance dose of arginine in uncomplicated malaria, to achieve average plasma arginine concentrations of ~600 uM (a plasma level ~4 times the Km of CAT2 transporters for cellular uptake of extracellular arginine). *Prior to the commencement of study 3, the Data Monitoring Committee will review the dosing and sampling schedule we will calculate from the pharmacokinetic-pharmacodynamic model generated in studies 1-2.* In addition, the target concentration (600 mcM) may need to be readjusted based on the results from studies 1 and 2.

*Design:* Randomised Concentration Controlled Trial.

*Treatment allocation:* Patients with uncomplicated malaria will be randomized to receive one of two treatments:

i) Standard RSMM antimalarial drug regimen for falciparum malaria (currently quinine) plus normal saline placebo (loading dose of 100 ml over 30 mins plus maintenance infusion using same volume in [ii] below).

ii) Standard RSMM antimalarial drug regimen for falciparum malaria (currently quinine) plus IV arginine: loading dose as 30 min infusion (see CRF) followed by maintenance infusion over 12 hours. The doses of arginine will be determined from the pharmacokinetic-pharmacodynamic model to maintain a plasma level of 600uM.

An independent statistician will use computer-generated randomization to generate blocks of patient numbers for each treatment.

*Sample size:* Extrapolating from similar concentration controlled trials, we estimate approximately 20 subjects in each of the two groups. Sample size calculation will require the results of the natural history of arginine/NO/NOx levels during malaria (study 1), and the maximal improvement and time course of improvement following administration (study 2). Therefore the final sample size will be calculated based on the results of studies 1 and 2. The sample size will be reviewed by the Data Safety and Monitoring Committee, and each of the relevant ethics Committees will be notified prior to commencement of Study 3 with confirmation of the number of patients.

*Patient numbering and randomization*:

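### Holding 600 uM for 12 h in Study 3 may exceed the total acid load behind the pH reassurance, and the last 4.5 h of infusion has no fixed bicarbonate check

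*Combined protocol and SAP*

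**What the plan says.** Study 3 fixes a concentration and a duration but no gram dose. Under Treatment allocation there is a 30-minute loading infusion and then maintenance over 12 hours: "The doses of arginine will be determined from the pharmacokinetic-pharmacodynamic model to maintain a plasma level of 600uM". The same section says the 600 uM target may be readjusted after studies 1 and 2, and that the Data Monitoring Committee will review dosing and sampling before Study 3 starts. The ethics committees are to be told the final number of patients; no similar commitment is made for the dose.

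The safety text sits under Study 2, but its heading covers both arginine studies: "Potential adverse effects (in study 2 and study 3) and study response". It calls the standard high dose of 30 g or more a "dose that will not be used in our studies". The potassium paragraph adds: "Moreover lower doses will be used in both of our studies than the 30g dose used in published studies". The introduction to the adverse effects, and again the Ethical issues section, speak of low arginine levels "combined with a dose well below the standard 30g IV dose used in other settings". The paragraph on pH gives the acid content ("Arginine hydrochloride contains H+ ions (4.75 mEq/g") and reports no pH change "despite infusion of 30g (much higher than we will use in this study". It sets a stop if venous bicarbonate falls below 15 mmol/L.

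For monitoring, the Study 3 Design section takes safety laboratory tests as in Study 2, with scope to optimise the sampling schedule, and continues observation for 24 hours after the infusion. Table 2 lists iSTAT draws at -60, 0, 30, 45, 60, 90, 180 and 480 minutes and the next morning (18-24 h). Its footnote places the Study 2 infusion at 0-30 minutes.

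**The concern.** A concentration target held for a fixed time implies a total dose once clearance is known, but the protocol never works that total out. Its safety argument was built around Study 2's 30-minute infusions of 3-12 g (up to 18 g if needed) and is then applied to a 12.5-hour infusion.

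What is at stake is total acid and chloride load. Peak-driven hyperkalaemia and hypotension are not the issue, because the maintenance rate is slow. The committees would be relying on a statement about acidosis that the planned target and duration may not honour. The bicarbonate stop is a real safeguard, but it can act only on a value measured while the infusion is running.

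**Working it through.** The plan states no Study 3 dose, so there is no figure to reproduce. The projection uses the protocol's own inputs.

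**Inputs**
- Clearance: 0.544-1.018 L/min (Background, clinical pharmacology).
- Target: 600 uM; maintenance: 720 min (Study 3).
- Endogenous level: 114 uM, the healthy Jayapura mean (Background). Patients' levels are said to be below normal, so subtracting 114 uM favours a low dose.
- Acid content: 4.75 mEq/g, which implies 1000/4.75 = 210.5 g/mol.

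**Maintenance dose** = clearance x (target - baseline) x time
- Low clearance: 0.544 x 486 uM x 720 min = 190.4 mmol. This is 40.1 g, 190 mEq and 40.1/12 = 3.3 g/h.
- High clearance: 1.018 x 486 uM x 720 min = 356.2 mmol. This is 75.0 g, 356 mEq and 75.0/12 = 6.2 g/h.

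**Sensitivity**
- Baseline 54 uM: 45-84 g. No baseline subtracted: 50-93 g.
- Loading dose, taking volume = clearance x half-life / ln 2 and the quoted half-life of 40-120 min: about 3-20 g more.
- Lowest variant, counted as free base (174.2 g/mol): 190.4 mmol = 33.2 g. The acid load is unchanged.

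**Against 30 g**
- Acid: 30 x 4.75 = 142.5 mEq. Ratios: 40.1/30 = 1.3 and 75.0/30 = 2.5.
- Rate: 30 g in 30 min is 60 g/h, against 3.3-6.2 g/h.
- Break-even clearance: (30/210.5) mol / (486 uM x 720 min) = 0.407 L/min, which is 25% below the quoted minimum (1 - 407/544). Any loading dose lowers it further.
- Target that 30 g could hold for 12 h: 478 uM at the lowest quoted clearance, 308 uM at the highest.
- Time that 30 g could hold 600 uM: 12 x 30/40.1 = 9.0 h, or 12 x 30/75.0 = 4.8 h.

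**Monitoring clock**, taking time 0 as the start of the load
- End of infusion: 0.5 + 12 = 12.5 h (750 min).
- Last Table 2 iSTAT during infusion: 480 min, which is 480/750 = 64% of the way through.
- Remaining infusion without a scheduled iSTAT: (750 - 480)/60 = 4.5 h. The next is at 18-24 h, after the infusion has ended.

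**The case against.** The strongest reply is that the 30 g statements are not about cumulative dose. They refer to the diagnostic dose that stimulates growth hormone release; the potassium paragraph describes it as a 30-minute infusion. Like for like, maintenance at 3.3-6.2 g/h is about a tenth of that rate or less. This stands. A reader might infer that Study 3 flatly breaks a promise to stay below 30 g, but the introductory, potassium and ethics statements do not support that.

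The pH paragraph is the exception, since acid load is a total. It says this study in the singular and sits in Study 2 text, but the heading above it extends to Study 3.

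A reader might also infer that 40-75 g is the planned dose, or an unsafe one. Neither follows. The quoted clearance comes from large doses in adults with normal arginine, with apparent non-linearity and extra renal excretion above the tubular threshold, so it may overstate clearance at 600 uM. The Background also says turnover may be raised in malaria, so the direction is uncertain. The dose comes from the studies 1-2 model, after committee review. Nothing in the documents shows that this acid rate causes acidosis in patients screened for bicarbonate of at least 20 and chloride of at most 106 meq/L. The upper part of the range overlaps what the protocol calls "again with very high dosing of 59-95g IV", but those patients had combined liver failure and renal impairment, and spironolactone use is named there as an exclusion. The overlap is no evidence of harm here.

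On monitoring, the pH paragraph promises serial real-time acid-base measurement, the schedule is still to be optimised, and the 8 h draw does fall within the infusion. So it would be wrong to infer that bicarbonate goes unmeasured during maintenance. What remains is that the stated default, followed on Table 2's clock, leaves the final 4.5 h uncovered.

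**Conclusion.** The point holds as a matter of internal consistency and safety monitoring; it is not an arithmetic error in the plan. At the quoted clearance, 600 uM for 12 h projects to 1.3-2.5 times the 30 g on which the acidosis reassurance rests, before the load. That reassurance carries over to Study 3 only if clearance in malaria is below about 407 ml/min, or the target or duration is reduced. The projection assumes steady state, one constant clearance and a 114 uM baseline. The monitoring gap assumes that Table 2's times are carried over unchanged from the start of the load.

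No unsafe dose has been set, and both matters can be settled at the review already planned before Study 3. No step in the visible text commits anyone to revisit the pH statement or to name a late draw; a dose cap in the case report form cannot be ruled out. I rate it minor to should-fix: a cheap safety improvement.

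**What to change.** 1. In the submission before Study 3, give the Data Monitoring Committee and both ethics committees the model-projected total dose (load plus maintenance) and its acid load. Then either cap the total by lowering the target or duration, or restate the 30 g comparisons, above all the one on pH, as applying to single short infusions. For scale, a 300 uM target over 12 h would need 15-29 g before the load, and 400 uM would need 24-44 g.

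2. For safety bloods, replace the reference to Study 2 with named iSTAT times covering the later part and the end of maintenance, for example about 10 h and 12.5 h from the start of the load.

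The cost is one calculation, some wording and two cartridges per patient: about 80 if done in both arms of about 20. At the 60 ul stated for the baseline iSTAT, two draws use 0.12 ml of tested blood. The Study 3 Design section already expects fewer pharmacokinetic and pharmacodynamic samples than Study 2, so this should fit within the 25 ml limit.

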Once the patient has a confirmed diagnosis of falciparum malaria, has fulfilled all the inclusion criteria, has none of the exclusion criteria and has given written informed consent to participate, he/she will be allocated the next code of the study.

Randomization will be carried out in groups of 10, and each code given a sealed opaque envelope which will contain that patients’ treatment group and which will only be opened when a patient has been allocated a code number.

*Design:*

Cannula insertion and baseline sampling will be performed as in study 2. Serial vital signs, clinical assessments, and laboratory parameters of safety will be measured as in Study 2 above. As appropriate, we will use the model generated from studies 1 and 2, and modeling of any electrolyte disturbances to optimize the sampling schedule ***which will result in a reduced total number of pharmacokinetic and pharmacodynamic blood samples required compared with study 2***. The maximum total volume of blood drawn will again be ≤25ml, but because of reduced numbers of samples will likely be less. In addition we will measure preliminary biomarkers of efficacy: fever and parasite clearance times, serial lactate levels, plasma levels of endothelial adhesion molecules, biomarkers of inflammation and effects on physiological parameters (including vascular function, gas transfer and physiological deadspace), with frequency again guided by results from studies 1 and 2. The effect on NO production will be examined by serial measures of plasma NOx/creat, and exhaled NO, and effect on oxidant stress, including serial plasma glutathione (GSH):oxidised glutathione (GSSG) ratios (by HPLC)61.

Observations will continue for 24 hours after the completion of the arginine infusion, with the final assessment at this time being identical to the final assessment in study 2.

*Outcomes:*

In the arginine-treated group there will be global improvements in both biochemical (including plasma NOx/creatinine, exhaled NO) and physiological markers (including brachial artery dilatation, hyperemic blood flow on Doppler and physiological deadspace).

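### Study 3 gives a saline placebo, but its envelopes disclose the treatment group and no stated step keeps it from patients or outcome assessors; a known block of 10 would also make some allocations foreseeable.

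*Combined protocol and SAP*

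**What the plan says.** All places are in the combined protocol and SAP.

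- **Arms** (Study 3, Treatment allocation): "Patients with uncomplicated malaria will be randomized to receive one of two treatments". The control arm receives quinine "plus normal saline placebo (loading dose of 100 ml over 30 mins plus maintenance infusion using same volume in [ii] below". The maintenance volume is therefore matched. For the loading infusion, the placebo volume is given and the arginine details are left to the CRF.
- **Sequence** (same section): "An independent statistician will use computer-generated randomization to generate blocks of patient numbers for each treatment".
- **Concealment** (Study 3, Patient numbering and randomization): a patient who is eligible and "has given written informed consent to participate, he/she will be allocated the next code of the study". Then: "Randomization will be carried out in groups of 10, and each code given a sealed opaque envelope". The envelope contains the "treatment group and which will only be opened when a patient has been allocated a code number".
- **Outcomes** (Study 3, Outcomes): plasma NOx/creatinine and exhaled NO, and physiological markers that include "brachial artery dilatation, hyperemic blood flow on Doppler and physiological deadspace".
- **Where and by whom** (footnotes to Tables 1 and 2; rationale for the brachial artery studies; Feasibility): endothelial and lung physiology and parasite counts are done at the hospital, on-site investigators are all to be trained in the brachial technique, and experienced collaborators supervise and assure quality.

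The supplied text does not say who opens the envelope, where, or who prepares the infusion. It does not say that patients, infusion staff, sonographers, breath-test operators or film readers are blinded, and it gives no emergency unblinding procedure. Nor does it call Study 3 open-label.

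**The concern.** A placebo protects outcome measurement only if the people who measure do not know the group. The written procedure puts the group in plain form inside the envelope and then says nothing about containing that knowledge. It could be followed to the letter by the person who later holds the ultrasound probe.

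Brachial dilatation and Doppler flow depend on how the image is acquired and measured. Deadspace and exhaled NO depend on patient effort and on which attempts are accepted; the exhaled NO procedure (Appendix 4) repeats the test until three valid readings are obtained. Bias that enters when a measurement is taken cannot be fully repaired in the analysis.

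Visible allocations have a second consequence. With one stated block size, staff who track past patients could foresee some later assignments. The entry criteria for Studies 2 and 3 leave room for judgement, for example on the indication for admission and on the absence of another cause of fever. A recruiter who foresees the next assignment could delay or decline to approach a patient.

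**Working it through.** **The plan's own figure.** About 20 per group, extrapolated from similar trials. No alpha, power, effect size or SD is stated, and the final calculation is deferred until Studies 1 and 2 are complete. The figure cannot be reproduced; it serves below as the provisional size.

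**1. Assessor bias**

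Inputs: n = 20 per arm (Study 3, Sample size). Assumed: two-sided 5%, no true effect, and a shift of s standard deviations in favour of arginine. The documents give no value for s, so a range is shown.

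Standard error of the difference in SD units = √(2/20) = 0.316.

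P(significant) = 1 − Φ(1.96 − s/0.316) + Φ(−1.96 − s/0.316)

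| Assumed shift s | s/0.316 | P(significant) |
|---|---|---|
| 0 | 0 | 5% |
| 0.2 SD | 0.63 | 9.7% |
| 0.3 SD | 0.95 | 15.8% |
| 0.5 SD | 1.58 | 35.3% |

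This is the normal approximation. A separate power calculation at 0.5 SD gave 34%.

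**2. Predictability of allocations**

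Inputs: blocks of 10 (Patient numbering and randomization). Assumed: 5:5 balance within each block, and block size and past allocations known to the recruiter.

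The last k allocations of a block are all certain when they belong to the same arm:

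P(k) = 2 × C(10−k, 5) / C(10, 5), with C(10, 5) = 252

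| k | P(last k or more certain) |
|---|---|
| 1 | 2 × 126/252 = 1.000 |
| 2 | 2 × 56/252 = 0.444 |
| 3 | 2 × 21/252 = 0.167 |
| 4 | 2 × 6/252 = 0.048 |
| 5 | 2 × 1/252 = 0.008 |

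The sum is 1.67 certain allocations per block of 10, or 4 × 1.67 = 6.7 of 40.

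Expected correct guesses per block under best guessing = 5 + 2⁹/252 − 0.5 = 6.53. That is 65%, or 26.1 of 40 against 20 by chance.

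**3. What varying the block size achieves**

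Simulated trials of 40 patients, past allocations visible, set of sizes known but their order hidden:

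| Block sizes | Certain in advance | Best-guess accuracy |
|---|---|---|
| Fixed 10 (exact) | 16.7% (6.7 of 40) | 65% |
| Random 4, 6, 8 | 2.3% (0.9 of 40) | 68% |
| Random 6, 8, 10 | 1.7% (0.7 of 40) | 66% |

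A smaller fixed block is worse: 25% certain at size 6 and 33% at size 4. Varying the size removes most of the certainty but does not lower guessing accuracy. Only hiding past allocations does that.

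**The case against.** The strongest reply is that silence is not a defect. A reader might infer that the envelope is opened at the bedside and that outcomes are assessed unblinded. The documents support neither. They name no place and no person, and someone with no part in assessment could open the envelope and prepare the infusion. The volume-matched placebo suggests that blinding was intended. The CRF and some pages were not available, and Study 3 was still to be designed in detail, with committee review of dosing, sampling and sample size. This stands as a limit on what can be claimed. It does not remove the gap, because the Study 3 allocation text is present and contains no such step.

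A second reply is that real safeguards exist: an independent statistician, sealed opaque envelopes, and a code issued only after eligibility and consent. These reduce selective enrolment. They do not stop a recruiter who can foresee the next code from holding a patient back.

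A third is that the exposed outcomes are only part of the evidence. A reader might infer that the move to severe malaria rests on operator-dependent measures. The Ethics section rests it on the data from Studies 1-3 as a whole, which include safety, pharmacokinetics and assays run off site (NOx, arginine and ICAM-1 in Darwin, oxidant markers in Sydney). Parasite films have a dedicated microscopist, and nothing shows that this person sees allocations. Exhaled NO is described as undemanding and has on-screen flow indicators, so it is less exposed than the ultrasound measures. All of this stands and narrows the point.

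**Conclusion.** The concern holds as a gap in the written method. Study 3 has a placebo but no stated blinding, and its one stated procedure discloses the group. On-site measures that depend on operator or effort are therefore exposed, above all brachial dilatation and Doppler flow.

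The size is conditional. The false-positive rates of about 10%, 16% and 34-35% illustrate assumed shifts of 0.2, 0.3 and 0.5 SD at 20 per arm; they do not estimate bias in this trial, and the largest should not be quoted alone. A reader might also infer that late allocations in a block are simply predictable. That needs 5:5 balance within blocks (not stated), knowledge of the block size, and visible past allocations. If all three hold, about one allocation in six is certain and best guessing is right about 65% of the time.

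The matter should be settled before Study 3 enrols. If the sponsor can show blinding procedures that already exist, it reduces to adding them to the protocol.

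**What to change.** In Study 3, Treatment allocation and Patient numbering and randomization:

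1. Name a person with no role in enrolment or outcome measurement who opens the envelope and prepares the infusions. Loading and maintenance infusions should have identical appearance and volume in both arms and carry the patient code only.
2. State that patients, and the staff who enrol, scan, run breath tests and read films, are kept unaware of the group.
3. Where ultrasound images are stored, have them read by code.
4. Have the independent statistician vary the block size and not disclose it to the site.
5. Keep a sealed copy of the allocation for emergency unblinding. The adverse-effect passages, which speak of the arginine infusion, must be reconciled with blinded bags.

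Items 1 and 2 are the main remedy, because they hide past allocations as well as protecting measurement. Item 4 alone would mainly remove the certain allocations.

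The cost is protocol wording and coded labels. The documents do not identify a preparer; the fix assumes one can come from existing staff, and that person cannot also take outcome measurements. Flushing or bedside K+ results may partly unmask the group, so blinding may be imperfect.
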